## 6. Missing data

- Missing items on baseline patient-reported measures replaced with **0** (conservative assumption).
- If >50% of items missing for a scale, no score calculated.
- No imputation planned.

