## EVALUATION

### Primary outcome measure

The primary outcome measure is the 3 month follow-up (T1) total score on the recently validated Danish version of the FCRI [13]. The FCRI is a 42-item self-report measure that includes subscales assessing FCR triggers, severity, psychological distress, functioning impairments, insight, reassurance, and coping strategies [48]. The FCRI has demonstrated high: internal consistency ( $\alpha=0.96$ ) [49], interclass correlation (0.84) [13] and convergent validity in large heterogeneous cancer survivor samples. Respondents rate the degree to which symptoms/issues affected them over the past month on a Likert scale ranging from 0 ('not at all' or 'never') to 4 ('a great deal' or 'all the time'). While there are potential issues with aggregating FCRI subscales [50], total FCRI score will be used as the dependent variable, as it closely reflects proposed features of clinically significant FCR; namely related distress, functional impact, and maladaptive coping[2], rather than the level of fear indicated by the FCRI-SF [50, 51]. Total scores can range from 0-168; higher scores indicate greater FCR morbidity. Level of FCR will be measured post-treatment (T0) and at follow-up after 3 (T1) and 6 (T2) months. Long-term effect will be evaluated after one year (T3). All electronic questionnaires will be sent out automatically through RedCAP.

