## 4. Outcomes

### Primary outcome

- Change in FCRI total score from baseline to 3 months.

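### Blank baseline items are scored 0, the lowest-fear FCRI answer, with no matching follow-up rule: this understates within-arm improvement and adds noise to the primary test, but does not bias the between-arm difference in expectation

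*Combined protocol and SAP*

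**What the plan says.** SAP section 6 (Missing data) has three lines. First: "Missing items on baseline patient-reported measures replaced with" 0, which the SAP describes as conservative. Second: "If >50% of items missing for a scale, no score calculated". Third: "No imputation planned". No item-level rule is given for any follow-up visit.

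The protocol (Primary outcome measure) describes the instrument: "The FCRI is a 42-item self-report measure", each item on a "Likert scale ranging from 0 ('not at all' or 'never') to 4", and "Total scores can range from 0-168; higher scores indicate greater FCR morbidity".

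SAP section 4 defines the primary outcome as "Change in FCRI total score from baseline to 3 months". Section 5.2 analyses it with paired t-tests within arm and a two-sample t-test on change scores between arms. Section 5.3 adds mixed models over time and indices of reliable and clinically significant change.

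The full FCRI is first collected at recruitment, when the survey score reaches the cut-off (protocol, Part 2, recruitment). In the protocol's Process of participation that questionnaire is step 4 and randomization is step 10.

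**The concern.** A skipped item is not a report of no fear, but the rule records it as one. The error goes one way, may cover up to half the scale, and enters the primary variable directly because baseline is subtracted from follow-up. As nothing is said about blank follow-up items, the two halves of the change score need not be scored alike. Zero-filling is also a form of single imputation, so section 6 is at odds with its own last line.

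At stake are the reported baseline level, the mean change in each arm with its paired test, the time effect in the mixed model, the individual-change indices, and the precision of the primary comparison in a trial whose target was cut to 68 participants (SAP, Update September 2023).

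**Working it through.** **Scale check.** 42 items × 0 = 0 and 42 items × 4 = 168. This reproduces the protocol's range, so the total is a plain sum and 0 is the floor of every item.

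**One participant.** Scored baseline = true baseline − sum of the true answers to the blank items. Change (follow-up − baseline) therefore moves upward, towards less improvement, by that same sum. The largest permitted number of blanks is 50% of 42 = 21.

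| Blank items | Answer 1 | Answer 2 | Answer 3 |
|---|---|---|---|
| 1 | 1 | 2 | 3 |
| 2 | 2 | 4 | 6 |
| 21 | 21 | 42 | 63 |

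For scale, the planning difference between group means is 3.5 points (protocol, Power calculation; SAP section 2). One participant with 21 blanks at value 2 moves the mean of a 27-person arm by 42/27 ≈ 1.6 points.

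**Variance and power.** Assumed, not from the documents: true baseline mean 84 (2 per item), SD 25 at both visits, correlation 0.6, true effect 12.5 points, and 20% of participants with k blanks. The 27 per arm comes from 68 less 20% dropout: 68 × 0.8 ≈ 54.

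With q = k/42 and p = 0.2, the error added to change is E = q × baseline for affected participants and 0 for the others.

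- Mean of E = p × q × 84
- Variance of true change = 2 × 625 × (1 − 0.6) = 500, so SD = 22.4
- Var(E) = q² × [p × (625 + 7,056) − (p × 84)²] = q² × 1,254
- Cov(true change, E) = q × p × (0.6 − 1) × 625 = −50q
- Variance of scored change = 500 + 1,254q² − 100q

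| k | Baseline too low by | Variance of change | SD | Power |
|---|---|---|---|---|
| 0 | 0 | 500 | 22.4 | 52% |
| 4 | 1.6 | 502 | 22.4 | 52% |
| 10 | 4.0 | 547 | 23.4 | 49% |
| 21 | 8.4 | 763 | 27.6 | 37% |

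Simulation under the same assumptions agrees: SD 22.2 to 23.2 and power 52% to 49% for 10 blanks; SD about 22.1 to 27.4 and power 52% to 37% for 21.

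**Chance imbalance.** The SD of the between-arm difference in mean E is √(2 × Var(E)/27). For k = 21, Var(E) = 313.5, which gives 4.8 points; a gap above 3.5 points then arises in about 47% of trials. For k = 10, Var(E) = 71.1, which gives 2.3 points and about 13%.

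**Direction of bias.** A separate item-level simulation (2,000 trials, 34 per arm, mean item near 2, blanks arising at random before allocation) gave these mean changes, control / intervention:

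| Participants with blanks; items blank | Complete data | Zero-filled | Difference between arms, complete → zero-filled |
|---|---|---|---|
| 10%; 10% | −7.8 / −11.0 | −6.9 / −10.2 | −3.2 → −3.3 |
| 30%; 10% | −7.9 / −11.1 | −5.4 / −8.6 | −3.2 → −3.2 |
| 30%; 30% | −7.8 / −11.1 | −0.3 / −3.5 | −3.3 → −3.2 |

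Within-arm improvement shrinks by about 0.9, 2.5 and 7.5 points. The difference between arms does not move. Scoring from the person's mean of answered items recovered the complete-data changes to within 0.01 point in every scenario.

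**The case against.** The best defence is that the rule does little harm where it matters most. Baseline is completed before allocation, so zero-filling lowers both arms equally in expectation. On the FCRI it understates improvement, which is a fair sense of conservative. Most forms are electronic, and whether they force an answer is not stated; if few items are blank, nothing of substance changes. The line against imputation may simply mean none beyond item scoring. All of this stands as a limit on size. None of it justifies scoring a blank as an absence of fear or leaving the follow-up rule undefined.

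Four stronger readings are tempting but unsupported.

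- **A biased treatment effect.** The order of events in the protocol rules this out in expectation.
- **Distortion of every change score.** Only participants with blank baseline items are affected.
- **False improvement on the quality-of-life scale, or an impossible 0 on perceived risk.** The protocol measures each of these with a single visual analogue item. A blank there is 100% missing, so the 50% rule gives no score. The documents do not give the EQ-5D-5L item coding, so nothing can be said about it.
- **Understated survey prevalence.** SAP section 1 confines the SAP to the randomized trial.

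The update of 10 January 2025 describes analyses already settled, so a new scoring rule would be post hoc. That calls for disclosure, not for keeping the zeros.

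**Conclusion.** The rule is unsound as scoring, inconsistent with the line that follows it, and silent on follow-up. For participants with blank baseline items it lowers the FCRI total or leaves it unchanged. It therefore biases within-arm change, the paired tests and the mixed-model time effect towards less improvement, and it can misclassify reliable and clinically significant change. For the primary between-arm comparison the cost is precision and possible chance imbalance.

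The size is not known, because neither document reports how many items were blank. The losses of about 3 and 15 percentage points of power are scenarios resting on the assumed mean, SD, correlation, effect and share of participants affected. With 4 blanks in 20% of participants, power is essentially unchanged. The January 2025 list of deviations does not mention this rule, so nothing shows that it was withdrawn.

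**What to change.** - Delete the zero rule. When at least 50% of a scale's items are answered, score from the person's mean of the answered items, by subscale for the FCRI, in the same way at baseline and every follow-up. Otherwise set the score to missing.
- Reword section 6 so that item scoring and the statement on imputation no longer conflict.
- Report the number of missing items by visit and arm, which will show at once whether the issue is trivial.
- Re-score and re-run any analysis that used zeros. Disclose this as a post hoc correction, with the zero-filled result shown as a sensitivity analysis.

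The two-sample test on change scores need not change. The cost is SAP wording, a change to the scoring code and a re-run; no new data are needed.

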## 7. Multiplicity

- No formal adjustments planned. Secondary and exploratory analyses considered hypothesis-generating.

## 8. Significance level and software

- 2-sided  $P < .05$  considered statistically significant.
- Analyses performed in **Stata 18** (StataCorp, College Station, TX).

### Update September 2023

Updated calculation: Based on published ConquerFear group trial data, 68 participants would be sufficient to detect a significant difference with 95% power and 20% dropout.

Reference: *ConquerFear-Group: A randomized controlled trial of an online-delivered group-based psychological intervention for fear of cancer recurrence in breast cancer survivors* Tauber et al, Psychooncology, Sep 2023.

Planned decision: The revised sample size was adjusted to reflect the larger expected effect size from prior data.

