## STATISTICAL PLAN

### Power calculation

The sample size is calculated for the primary outcome FCR measured by the FCRI. To detect a standardised mean difference in FCR (Cohen's  $d = 0.5$ , group difference of 3,5 and a standard deviation of 7) with 90 % power and two-sided  $\alpha = 0,05$  with two-sided t-test a sample size of 246 participants is desired. With a realistic dropout of 30 %, 350 participants are required in each group, and it seems realistic to recruit this as a minimum among the estimated number of eligible participants.

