## RESEARCH PLAN

The protocol is part of a PhD project at the University of Southern Denmark planned from January 1st 2020 and the following 5 years parallel with specialist training, see Fig. 4 for elaboration.

Key dates:

May 2020: Extract data from RKKP

September 2020: Launch survey

October 2020: Inclusion of first participant

April 2022: RCT finish

May 2023: Final 1-year follow-up

January 2024: Extraction of retrospective economic data

Fig. 4, research and study plan

| Research and study plan                                                              |      |    |      |    |    |    |      |    |    |    |      |    |    |    |      |    |    |    |      |    |    |    |      |    |    |  |  |
|--------------------------------------------------------------------------------------|------|----|------|----|----|----|------|----|----|----|------|----|----|----|------|----|----|----|------|----|----|----|------|----|----|--|--|
|                                                                                      | 2018 |    | 2019 |    |    |    | 2020 |    |    |    | 2021 |    |    |    | 2022 |    |    |    | 2023 |    |    |    | 2024 |    |    |  |  |
| Activity                                                                             | Q4   | Q1 | Q2   | Q3 | Q4 | Q1 | Q2   | Q3 | Q4 | Q1 | Q2   | Q3 | Q4 | Q1 | Q2   | Q3 | Q4 | Q1 | Q2   | Q3 | Q4 | Q1 | Q2   | Q3 | Q4 |  |  |
| Preparation studies
- Protocol
- Ethics
- Review
- Fundraise
- REDCap |      |    |      |    |    |    |      |    |    |    |      |    |    |    |      |    |    |    |      |    |    |    |      |    |    |  |  |
| Specialist training                                                                  |      |    |      |    |    |    |      |    |    |    |      |    |    |    |      |    |    |    |      |    |    |    |      |    |    |  |  |
| Platform work
- Translate
- Test                                               |      |    |      |    |    |    |      |    |    |    |      |    |    |    |      |    |    |    |      |    |    |    |      |    |    |  |  |
| miniSCAN education & training                                                        |      |    |      |    |    |    |      |    |    |    |      |    |    |    |      |    |    |    |      |    |    |    |      |    |    |  |  |

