## 2. Sample size

- **Initial a priori calculation:** 350 participants required to detect a standardized mean difference of Cohen's  $d = 0.50$  (mean difference = 3.5; SD = 7), with 90% power, 2-sided  $\alpha = 0.05$ , and 30% dropout.

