### Update 10 Jan 2025

#### Deviations from SAP

Several analyses specified in the statistical analysis plan were not conducted due to limitations in sample size and data availability.

- Per-protocol analyses were not performed, as the five participants classified as passive users (<2 modules completed) did not contribute outcome data, precluding meaningful subgroup comparison.
- Mediator analyses (eg, illness uncertainty, perceived risk of recurrence, negative beliefs about worry) were not conducted because of insufficient statistical power.
- Predictor analyses of demographic and clinical moderators (eg, age, gender, disease stage, treatment type) were omitted for the same reason.
- Economic analyses, originally planned using registry data, were not undertaken due to lack of power and feasibility constraints.

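### The September 2023 claim of 95% power with 68 participants rests on an unstated effect of about d = 1.0; at the only effect size the documents give, d = 0.5, power is about 44%

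*Combined protocol and SAP*

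**What the plan says.** The SAP's section 2 gives the initial calculation as "350 participants required to detect a standardized mean difference" of 0.50 ("mean difference = 3.5; SD = 7), with 90% power"), two-sided alpha 0.05 and 30% dropout. The protocol's Power calculation uses the same effect, a "group difference of 3,5 and a standard deviation of 7", and the same 30% dropout.

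The SAP's Update September 2023 then states, "Based on published ConquerFear group trial data", that "68 participants would be sufficient to detect a significant difference with 95% power and 20% dropout". Its stated reason is that "The revised sample size was adjusted to reflect the larger expected effect size from prior data". It gives no standardised effect, mean difference, SD, test or alpha, does not say whether 68 is a total or per arm, and does not report power at d = 0.5. The source it cites is, by its title, an online group intervention in breast cancer survivors.

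The protocol's Research plan lists "April 2022: RCT finish" and puts the final one-year follow-up in May 2023.

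**The concern.** Power has meaning only for a named effect. Here the effect is missing, while the power rises from 90% to 95% and the sample falls to 68. The only effect a reader can find in the documents is d = 0.5, so the natural but mistaken inference is that 68 participants give 95% power for it.

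The primary conclusion is at stake. With an advertised 95% power, a null result looks like good evidence that the intervention does not work. If power for the original target is below one half, a null result says little. A significant result from a sample this small will also tend to overstate the effect, because only large observed differences reach significance.

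**Working it through.** **Inputs.** N = 68, power 95%, dropout 20% (Update September 2023). Allocation 1:1 (protocol, Study design). Two-sided alpha 0.05 (protocol, Statistical analysis; SAP section 8). Two-sample t-test on change scores (SAP 5.2). No imputation (SAP section 6), so dropouts contribute nothing to that test. Stated effect d = 3.5/7 = 0.5 (protocol, Power calculation; SAP section 2).

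**Method.** Evaluable number = N × (1 − dropout). With n per arm, the noncentrality is δ = d√(n/2) on 2n − 2 degrees of freedom, and power is the probability that the noncentral t exceeds the critical value.

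**1. Reproduce 68.** Because d is not given, solve for it.
- 68 × 0.8 = 54.4, about 27 per arm. With 52 degrees of freedom the critical value is 2.007, and 95% power needs d = 1.00 (0.98 by normal approximation).
- Forward check: at d = 1.0 and 95% power the t-test needs 53.98 evaluable, that is 54. Then 54/0.8 = 67.5, rounded up to 68. The plan's figure is reproduced.

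**2. Power at the stated effect.** n = 27, d = 0.5: δ = 0.5 × √13.5 = 1.84, power 43.8% (45.1% by normal approximation).

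**3. With the protocol's 30% dropout.** 68 × 0.7 = 47.6, or 23.8 per arm. Power is 39.3% at d = 0.5 and 92.2% at d = 1.0.

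**4. Precision.** The 95% CI half-width is 2.007 × √(2/27) = 0.55 SD. An interval centred on zero would still include d = 0.5.

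**5. Other readings of 68** (effects on the scale that is tested):

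| Reading | d needed for 95% power | Power at d = 0.5 |
|---|---|---|
| 68 randomised in total, 20% dropout | 1.00 | 44% |
| 68 evaluable in total | 0.89 | 53% |
| 68 per arm, 20% dropout | 0.70 | 73% |

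**6. Which SD is 7?** The documents do not say whether it is the SD of change or of the follow-up score. If it is the follow-up SD, with equal variances and baseline/follow-up correlation r, the change-score SD is 7√(2(1 − r)) and the effect tested is 0.5/√(2(1 − r)). The documents give no such r, so these values are assumptions, with 27 per arm:

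| Assumed r | Effect tested | Power |
|---|---|---|
| 0.3 | 0.42 | 33% |
| 0.5 | 0.50 | 44% |
| 0.7 | 0.65 | 64% |

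To reach 95% in this way, 0.5/√(2(1 − r)) must equal 1.0, so r = 1 − 0.25/2 = 0.875. If 68 is per arm, the corresponding value is about 0.75.

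**7. What d = 0.5 would need.** 95% power requires 105 per arm, 210 evaluable; 210/0.8 = 262.5, so 263 randomised.

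**The case against.** The strongest reply is that no arithmetic error is shown: 68 follows exactly from d = 1.0, and the update openly says that it assumes a larger effect than before. That stands. The defect is an unreported assumption, and a sponsor may change its assumed effect. But the update neither quantifies the new effect nor says that d = 0.5 has ceased to matter, so the 95% cannot be interpreted as written.

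It can also be said that d = 1.0 and 44% depend on how 68 and the SD are read. That stands too, which is why the ranges are shown.

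Several stronger readings are tempting, and the documents do not support them:

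- *The re-sizing was a post-hoc justification.* September 2023 is later than the planned dates in the Research plan, but those are plans. The documents give no actual recruitment or follow-up dates and do not say who had seen data. The timing supports a request for disclosure, not a finding about motive.
- *Recruitment fell short.* No shortfall is stated, and the update gives a different reason.
- *The cited trial does not support the effect.* Its figures are not in the documents. The group format and breast cancer population differ from this trial, but both interventions are delivered online.
- *The dropout was cut to 20% without any reason.* The reference to the published trial may cover the dropout as well as the effect.
- *The sponsor has conceded low power for the primary outcome.* The January 2025 update says that mediator analyses "were not conducted because of insufficient statistical power" and omits predictor analyses for the same reason. It makes no statement about the power of the primary comparison.

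**Conclusion.** The point holds as one of undisclosed assumption and misleading power. On the natural reading (68 randomised in total, 1:1, two-sided t-test at 0.05, 20% dropout, d on the change-score scale), 95% power requires d of about 1.0. At d = 0.5 power is about 44%, or about 39% with 30% dropout.

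A reader might infer that 1.0 is the only possible value. It is not: the implied effect is 0.89 if 68 is the evaluable total and 0.70 if it is per arm. With d = 0.5 on the scale tested, none of these readings gives 95% power. If SD = 7 refers to follow-up scores, power for 68 in total runs from 33% to 64% over assumed correlations of 0.3 to 0.7. Reaching 95% would need a correlation of about 0.875, for which the documents provide no basis.

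**What to change.** Keep the September 2023 entry as the audit trail. Add a dated addendum to the SAP, and carry it into the report, that:

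- states the effect size behind 68, the SD and whether it refers to change or follow-up scores, the source of the 20% dropout, and whether 68 is a total or per arm;
- restates the power: if 68 is the total randomised, 95% only for d of about 1.0, and about 44% for the originally targeted d = 0.5 (about 39% with 30% dropout), with a 95% CI half-width of about 0.55 SD. If the sponsor's inputs differ, recompute these figures from them;
- says when the re-sizing was decided relative to actual recruitment and follow-up, and whether those deciding had seen outcome data by arm;
- commits to reporting a non-significant result whose CI includes d = 0.5 as inconclusive, not as evidence of no effect.

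The addendum should not assert a recruitment shortfall, nor cite 246 as the planned size. The SAP gives 350 participants and the protocol 350 in each group; 246 is the protocol's figure before its dropout step.

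The cost is wording in the SAP and report, and a less favourable power statement. No further participants or data are needed.

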### Update 10 Jan 2025

#### Deviations from SAP

Several analyses specified in the statistical analysis plan were not conducted due to limitations in sample size and data availability.

- Per-protocol analyses were not performed, as the five participants classified as passive users (<2 modules completed) did not contribute outcome data, precluding meaningful subgroup comparison.
- Mediator analyses (eg, illness uncertainty, perceived risk of recurrence, negative beliefs about worry) were not conducted because of insufficient statistical power.
- Predictor analyses of demographic and clinical moderators (eg, age, gender, disease stage, treatment type) were omitted for the same reason.
- Economic analyses, originally planned using registry data, were not undertaken due to lack of power and feasibility constraints.

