**Part 2 b, randomization**

*If randomized to augmented TAU:* The control group is described as “augmented” as the diagnostic telephone interview exceeds standard treatment. Furthermore, if randomized to augmented TAU the information letter (appendix 7. Informationsbrev) send to E-boks will include a reference to a website with a non-guided, publicly available E-learning program in cancer rehabilitation hosted by the Region of Central Jutland (livogkraeft.rm.dk). The website includes, besides a written material, self-help instructions for meditation. Use of the website will not be monitored.

*If randomized to TG-iConquerFear:* The information letter (Appendix 7. Informationsbrev) will contain a link to enter the platform directly. The assigned therapist will be informed simultaneously.

Both groups will follow standard surveillance according to national guidelines for cancer recurrence at a surgical or oncological department, which may include colonoscopy and/or CT scans. The municipality is responsible for rehabilitation and offers limited access to physical exercise, yoga, dieticians, psychologists, sexologists etc.

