### **Part 4, intervention**

The theoretical frame of iConquerFear[29] is based on the Common-Sense Model (CSM) of illness, the Self-Regulatory Executive Function model (S-REF; targets metacognitions) and Relational Frame Theory (RFT; theoretical basis for Acceptance and Commitment Therapy). The intervention includes elements of attention training, increasing metacognitive awareness, acceptance & mindfulness, promotion of expedient screening behaviour, and values-based goal setting. The platform is accessed through secure log-on and comprises 5 modules containing educational text, interactive exercises, short videos featuring doctors, therapists and patients' perspectives, see Fig. 3.

The Australian version of iConquerFear is completely self-directed.

The Danish version of iConquerFear will contain a messenger-function on the intervention dashboard, allowing the participant and therapist to communicate asynchronously (TG-iConquerFear). The participant is guided through the sessions by minimum weekly contact with an experienced therapist. The therapist will motivate, answer questions and give feedback on written material and exercises. The amount of contact will be recorded and explored as a moderator of intervention efficacy. Should any cancer-related questions occur, an oncologist or surgeon will be involved as a consultant to the therapists.

The programme can monitor adherence, dropouts and track log-ins and activity. A purpose-developed single-item questionnaire within the TG-iConquerFear will each week ask for level of engagement[47]. Participants who do not adhere to, or withdraw from, the intervention will be contacted by telephone and asked why. These participants will be asked if they would be willing to complete a post-intervention assessment and all follow-up assessments to aid intervention evaluation. Therapist assistance is scheduled to last 10 weeks, but the participants will have free access to the platform for another 6 months.

In case of recurrence during the 10 weeks of intervention, the participant will be excluded from analysis, but may continue in the programme.

Fig. 3, iConquerFear curriculum content

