### Statistical analysis

A flowchart of participants and dropouts following the CONSORT guidelines will be drawn.

STATA will be used for all statistical analyses. All statistical tests will be two-sided (level of significance = 0.05).  $\chi^2$ -tests will be performed on all follow-up data to analyse proportions of participants above or below the clinical cut-off.

The influence of the intervention will be analysed for the primary outcome and for all secondary outcomes. Linear mixed effects models will be used to analyse longitudinal differences between intervention and control group. Association with functional disorders (health anxiety and bodily distress symptom) and psychiatric disorders (anxiety and depression) will be evaluated with adjusted and unadjusted linear regressions analyses on baseline data.

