## 3. Analysis populations

- **Intention-to-treat (ITT):** All randomized participants analyzed according to their assigned group, regardless of adherence. The ITT population will form the primary analysis set.
- **Per-protocol (PP):** All participants who adhere to the intervention (>2 of 6 modules completed in TG-iConquerFear, or equivalent engagement with control condition). PP analyses will be performed to examine the robustness of ITT findings.
- **Exploratory subgroups:** Completers (6 modules) versus partial completers (2–5 modules). Analyses will also explore differences in demographic and psychosocial characteristics between subgroups.

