### 5.2 Primary analysis

- Within-group changes from baseline to follow-up assessed with paired *t*-tests.
- Between-group differences in mean change scores tested using 2-sample *t*-tests (or non-parametric equivalent if assumptions violated).
- Effect size (Cohen's *d*) and 95% CI reported for between-group differences at 3 months.

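### The primary analysis called intention-to-treat is an available-case t-test that leaves out the five passive users, and nothing planned bounds the effect on the estimate

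*Combined protocol and SAP*

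**What the plan says.** SAP section 3 defines the intention-to-treat set as "All randomized participants analyzed according to their assigned group, regardless of adherence" and makes it the primary analysis set.

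SAP section 5.2 gives the primary test: "Between-group differences in mean change scores tested using 2-sample" t-tests, or a non-parametric equivalent. SAP section 6 adds "No imputation planned".

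The SAP update of 10 January 2025, under Deviations from SAP, drops the per-protocol analysis because "the five participants classified as passive users (<2 modules completed) did not contribute outcome data".

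Three other places bear on this:

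- The protocol (Part 4, intervention) intended to telephone non-adherers and ask them to complete the post-intervention and follow-up assessments. The data on such people were therefore meant to be collected.
- SAP section 3 defines the per-protocol set as more than 2 of 6 modules, or comparable engagement in the control arm. The protocol says that the platform "comprises 5 modules containing educational text" and, of the control website, "Use of the website will not be monitored".
- The protocol (Statistical analysis; Dropout analysis) plans a CONSORT flowchart and a comparison of participants with dropouts. SAP section 5.5 plans a logistic regression of dropout, and SAP section 5.3 a linear mixed model as a secondary analysis.

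**The concern.** A change score exists only for someone with a 3-month FCRI total. With no imputation, the t-test is an analysis of available cases whatever the set is called, and the definition in SAP section 3 is met only if nobody lacks a 3-month score. The 2025 update shows that some people do, and that in the intervention arm they include those who hardly used the programme.

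What is at stake is the question the primary result answers. Intention-to-treat estimates the effect of being assigned to the programme, non-users included. If the non-users are absent because they have no data, the result describes the people who stayed and responded, and the two arms compared need no longer be exchangeable. The per-protocol analysis was meant as the robustness check. It was dropped because the five have no data, but for the same reason they are missing from the primary analysis. No analysis in the SAP asks how the primary estimate would change under plausible outcomes for them.

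**Working it through.** **Is there a plan figure to reproduce?** The documents give no effect estimate and no count randomised, so there is no plan figure for this bias. The planning figures supply only a scale.

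- Protocol, Power calculation: "group difference of 3,5 and a standard deviation of 7", so d = 3.5/7 = 0.50. A t-test at two-sided 0.05 and 90% power needs 86 per arm, 172 in total; 172/0.70 = 246. The protocol's 246 is thus reproduced, with the 30% dropout already in it. The 350 appears only if dropout is applied again (246/0.70 = 352). The present point does not depend on this.
- SAP, Update September 2023: 68 participants, 95% power, 20% dropout, effect size not stated. 68 × 0.80 = 54 evaluable, 27 per arm, which implies d of about 1.00.

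**Who can enter the primary test.** Sections 5.2 and 6 of the SAP together require an observed 3-month score. The five passive users have none. They must be intervention participants, since modules exist only there.

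**Model for the size.** Let n be the number randomised to the intervention, q = 5/n, D the available-case effect, and r the benefit of the five as a fraction of the benefit in those observed. Assume that the control arm is unbiased for the whole intervention arm, that the five are the only loss that matters, and that the SD is unchanged. Then

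effect of assignment = (1 − q)·D + q·r·D = D·[1 − q(1 − r)]

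overstatement = 1/[1 − q(1 − r)] − 1

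**Varying the benefit of the five, with n = 34** (68 at the 1:1 ratio in the protocol; an assumption). q = 5/34 = 0.147.

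| Benefit of the five | Factor | D = 1.00 becomes | D = 0.50 becomes | Available-case effect is |
|---|---|---|---|---|
| None (r = 0) | 0.853 | 0.85 | 0.43 | 17% too large |
| Half (r = 0.5) | 0.926 | 0.93 | 0.46 | 8% too large |
| Same (r = 1) | 1.000 | 1.00 | 0.50 | correct |
| 1.5 times (r = 1.5) | 1.074 | 1.07 | 0.54 | 7% too small |

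No benefit is not the extreme case. If the five ended 0.5 SD worse than control (an arbitrary value), D = 1.00 would become 0.853 − 0.147 × 0.5 = 0.78.

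**Varying the arm size, with r = 0.**

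| n | q | Factor | Overstatement |
|---|---|---|---|
| 25 | 20.0% | 0.800 | 25% |
| 30 | 16.7% | 0.833 | 20% |
| 34 | 14.7% | 0.853 | 17% |
| 40 | 12.5% | 0.875 | 14% |
| 50 | 10.0% | 0.900 | 11% |
| 175 (350 at 1:1) | 2.9% | 0.971 | 3% |

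The last row shows why five people matter more at a target of 68 than at one of 350.

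**The case against.** The strongest reply is that the direction of bias is unknown. The documents do not say how many were randomised, how many controls were lost, why anyone was lost, or how the five fared. If the five benefited like the others there is no bias from their loss; if they stopped because they felt better, the estimate is too small. Informative loss in the control arm could offset or add to the effect. This stands in full, and it limits the claim to a possible overstatement. That people who completed fewer than two modules gained little is plausible, but it is an assumption.

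A second reply is that the plan would expose selective loss: the flowchart, the comparison of participants with dropouts, and the dropout regression all bear on it, and the protocol tried to retain non-adherers. This also stands. A reader who says that nothing planned would reveal the problem goes too far. These analyses describe who was lost; they do not show how far the primary estimate could move.

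A third reply is that the mixed model uses everyone. It helps only in part. On the update's wording the five contribute baseline data at most, so their later course is inferred under missing at random, which is the assumption in doubt.

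A reader might also infer that the primary result is in effect a per-protocol analysis. The documents do not support that. The per-protocol set needs more than two modules, whereas passive means fewer than two, so someone with exactly two modules and a 3-month score is in the t-test but outside the per-protocol set. The t-test applies no engagement filter to controls, and with website use unmonitored no control per-protocol set could be formed.

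**Conclusion.** The point holds as a mismatch between label and method. The primary test is an available-case analysis; the intention-to-treat property stated in SAP section 3 is not delivered; the known loss in the intervention arm is related to adherence; and no planned analysis bounds the consequence.

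The estimate may overstate the effect of assignment. Under the stated assumptions (34 in the arm, unbiased control arm, no benefit in the five) the overstatement is 17%, with 25% to 11% for arms of 25 to 50. It is zero with equal benefit and reverses with greater benefit. The 68 behind the 34 is a planning figure that already allows for dropout, not a count of people randomised, so these numbers show scale and are not an estimate of the actual bias.

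Two stronger statements are tempting and not supported: that the result does overstate the effect, and that comparable low-engagement controls all remain in the analysis. Nothing in the documents reports control-arm follow-up or engagement.

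**What to change.** 1. Relabel the t-test in SAP section 5.2 as an available-case analysis. Report, by arm, the numbers randomised and analysed at 3 months, with reasons for every absence. These reasons should include any exclusion for recurrence during the 10 weeks, which the protocol removes from analysis and SAP section 3 does not mention.
2. Add a sensitivity analysis on all randomised participants. For intervention participants without a 3-month score, use multiple imputation based on the control arm, conditional on the baseline FCRI total, which is collected before randomisation. Then shift the imputed values by increasing deltas and report the shift at which the conclusion changes. Because the 2025 update already records which analyses were not done, label this as added after the fact; do not substitute it for the primary test.
3. Report the mixed model already planned, including every randomised participant with baseline data, with its 3-month contrast. Present it as a supporting analysis under missing at random.
4. If a replacement for the per-protocol analysis is wanted, do not divide the available-case difference by the proportion completing modules; that would inflate it further. A complier-average estimate is usable only if its numerator includes the five.
5. Separately, reconcile the module count: 5 in the protocol, 6 in SAP section 3.

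The cost is SAP wording and some extra analysis in Stata, with no new data collection. The estimate may become smaller or less certain.
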